## Abstract

**Background:**

Acute lung injury (ALI) is a common devastating clinical syndrome characterized by life-threatening respiratory failure requiring mechanical ventilation and multiple organ failure. There are *in vitro*, animal studies and pre-clinical data suggesting that statins may be beneficial in ALI. The Hydroxymethylglutaryl-CoA reductase inhibition with simvastatin in Acute lung injury to Reduce Pulmonary dysfunction (HARP-2) trial is a multicenter, prospective, randomized, allocation concealed, double-blind, placebo-controlled clinical trial which aims to test the hypothesis that treatment with simvastatin will improve clinical outcomes in patients with ALI.

**Methods/Design:**

Patients fulfilling the American-European Consensus Conference Definition of ALI will be randomized in a 1:1 ratio to receive enteral simvastatin 80 mg or placebo once daily for a maximum of 28 days. Allocation to randomized groups will be stratified with respect to hospital of recruitment and vasopressor requirement. Data will be recorded by participating ICUs until hospital discharge, and surviving patients will be followed up by post at 3, 6 and 12 months post randomization. The primary outcome is number of ventilator-free days to day 28. Secondary outcomes are: change in oxygenation index and sequential organ failure assessment score up to day 28, number of non pulmonary organ failure free days to day 28, critical care unit mortality; hospital mortality; 28 day post randomization mortality and 12 month post randomization mortality; health related quality of life at discharge, 3, 6 and 12 months post randomization; length of critical care unit and hospital stay; health service use up to 12 months post-randomization; and safety. A total of 540 patients will be recruited from approximately 35 ICUs in the UK and Ireland. An economic evaluation will be conducted alongside the trial. Plasma and urine samples will be taken up to day 28 to investigate potential mechanisms by which simvastatin might act to improve clinical outcomes.

**Trial registration:**

Current Controlled Trials ISRCTN88244364.

## Background

Acute lung injury (ALI) is a common devastating clinical syndrome characterized by life-threatening respiratory failure requiring mechanical ventilation and multiple organ failure. ALI is defined by the American-European Consensus Conference [1] as the acute onset of hypoxia (PaO2:FiO2 ratio of <40 kPa) and bilateral infiltrates on a chest radiograph in the absence of cardiogenic causes of pulmonary edema. ALI occurs in response to a variety of insults. It affects all age groups; has a mortality of approximately 30% to 40% [2-5] and causes a long-term reduction in quality of life for survivors [6]. ALI has significant resource implications, prolonging ICU and hospital stay, and requiring rehabilitation in the community with many survivors unable to return to work 12 months after hospital discharge [7,8].

### Rationale for statins in the treatment of ALI

Hydroxymethylglutaryl coenzyme A (CoA) reductase inhibition with statins is a potential novel therapeutic strategy to treat ALI. Statins have been shown to modify a number of the underlying mechanisms that mediate this process both *in vitro* and *in vivo* in animal models of ALI [9]. In an observational study in patients with ALI, after adjusting for potential confounding factors, patients receiving statins had a lower probability of death with an odds ratio 0.27, although this failed to reach statistical significance [4]. In healthy volunteers, pre-treatment with simvastatin for four days results in attenuation of both pulmonary and systemic inflammatory responses in a model of ALI induced by lipopolysaccharide (LPS) inhalation [10]. In this human model, statins reduced pulmonary neutrophilia, pro-inflammatory cytokines and proteases as well as systemic C-reactive protein (CRP).

A single center, randomized, double-blind, placebo-controlled study, Hydroxymethylglutaryl-CoA reductase inhibition with simvastatin in Acute lung injury to Reduce Pulmonary dysfunction (HARP), investigated simvastatin (80 mg for up to 14 days) in 60 patients with ALI [11]. This study provided proof of concept data of a beneficial effect with significant improvements in non-pulmonary organ dysfunction, as measured by the Sequential Organ Failure Assessment (SOFA) score as well as a trend to improvements in pulmonary dysfunction, as measured by the oxygenation index (OI), respiratory system compliance and lung injury score in the simvastatin-treated group. Importantly, simvastatin 80 mg was well tolerated with no increase in adverse events. In addition, pulmonary IL-8 and systemic CRP were lower in the simvastatin-treated group. The study was not designed or powered to show an effect of simvastatin on clinical outcomes. The findings from these studies helped inform the design of two large clinical trials. In the US, the National Heart, Lung, and Blood Institute Acute Respiratory Distress Syndrome (ARDS) network is currently conducting a trial of rosuvastatin for infection-related ALI (SAILS study; NCT00979121). The aim of the HARP-2 trial is to test the hypothesis that treatment with enteral simvastatin 80 mg would improve clinical outcomes in patients with ALI irrespective of etiology. A second objective is to determine the effects of simvastatin treatment on biological mechanisms important in the development of ALI and assess whether the response to simvastatin is determined by genetic polymorphisms.

## Methods/Design

The Belfast Health and Social Care Trust (BHSCT) is the sponsor for the UK sites and the National University of Ireland (NUI) Galway is the sponsor for the Irish sites. The trial will be conducted in accordance with the ethical principles that have their origin in the Declaration of Helsinki. The protocol is approved by the Office for Research Ethics Committees, Northern Ireland for UK sites (10/NIR02/36) and by the institutional Research Ethic Committee for each site in Ireland. The trial is registered on the International Standard Randomized Controlled Trial Registry (ISRCTN88244364) and with the European Union Drug Regulating Authorities Clinical Trials database (2010-020763-20). The study is funded by the Efficacy and Mechanism Evaluation (EME) program (http://www.eme.ac.uk). This study is also funded in Ireland by the Health Research Board. The HSC R&D, Public Health Agency in Northern Ireland and the Intensive Care Society of Ireland have also provided additional funding. The trial is being coordinated by the Clinical Research Support Centre (CRSC) as the Clinical Trials Unit (CTU) (http://www.crsc.hscni.net). The trial will comply with the principles of good clinical practice (GCP) and will be carried out in accordance with applicable legislation and the standard operating procedures of the CRSC. The trial will be reported in line with the Consolidated Standards of Reporting Trials (CONSORT) 2010 guidelines [12].

### Outcome measures

The primary outcome measure is ventilator free days (VFDs). VFDs will be defined as the number of calendar days from the time of initiating unassisted breathing to day 28 after randomization, assuming survival for at least two consecutive calendar days after initiating unassisted breathing and continued unassisted breathing to day 28. If a patient returns to assisted breathing and subsequently achieves unassisted breathing prior to day 28, VFDs are counted from the end of the last period of assisted breathing. If a patient was receiving assisted breathing at day 27 or dies prior to day 28, VFDs will be zero [13]. Unassisted breathing is defined as being extubated with supplemental oxygen or room air; or open T-tube breathing; or tracheostomy mask breathing; or continuous positive airway pressure (CPAP) ≤5 cm H_2_0 without pressure support. Sites are advised that usual CPAP or (BIPAP) Bilevel positive airway pressure solely for sleep-disordered breathing management is not defined as assisted breathing. Patients receiving pressure support via non-invasive ventilation for any other reason will be defined as receiving assisted ventilation. Patients transferred to another hospital or other health care facility will be followed to day 28 to assess this endpoint.

There are a number of secondary outcomes for this clinical trial which include clinical outcomes, safety, health economic evaluation and biological mechanisms.

The secondary clinical outcomes are change in OI from baseline to day 3, 7, 14 and 28; change in SOFA score from baseline to day 3, 7, 14 and 28; non pulmonary organ failure free days (defined as the number of days in the first 28 days after randomization that the patient received no cardiovascular, renal, liver or neurological support as defined by the Critical Care Minimum Dataset [14]); all cause mortality 28 days post randomization; mortality at (first) discharge from critical care; mortality at (first) discharge from hospital and mortality at 12 months post randomization.

### Safety

The frequency with which the following events occur will be reported: (1) creatine kinase (CK) >10 times the upper limit of normal; (2) alanine transaminase (ALT)/aspartate aminotransferase (AST) >8 times the upper limit of normal; (3) need for renal replacement therapy in patients with CK elevated >10 fold; and (4) serious adverse events (SAEs) and occurrence of suspected unexpected serious adverse reactions (SUSARs). Safety monitoring (CK and liver transaminases) is undertaken at days 3, 7, 14, 21 and 28.

### Health economic evaluation

Health related quality of life (HRQoL) will be measured using the EuroQol 5 dimension questionnaire (EQ-5D) [15]. Data will be collected at hospital discharge and 3, 6 and 12 months post randomization. Resource utilization (critical care and hospital length of stay and health service contact) will be recorded at 6 and 12 months post randomization.

### Biological mechanisms

A translational study of biological markers of inflammation and lung injury to provide insight into the mechanism of action of simvastatin in ALI will be undertaken. Blood and urine will be taken on days 0, 3, 7, 14 and 28 while patients continue to receive the study drug. Plasma from 20 ml of heparinized blood along with aliquots of urine will be stored at −70°C until analysis. We will measure neutrophil activation, proinflammatory cytokines and adhesion molecule expression and nuclear factor kappa B (NFkB) activation. Furthermore, we will measure cell-specific indices of activation and injury to the alveolar epithelium and endothelium, as well as the lung extracellular matrix degradation. Blood will also be collected for genetic testing to assess whether response to simvastatin is determined by genetic polymorphisms.

It is recognized that it may not be possible to collect plasma and urine samples from all patients and in the event that samples are not collected, this will not be recorded as a protocol violation.

### Eligibility criteria

Patients will be eligible for the trial if they fulfill the following criteria:

1. Receiving invasive mechanical ventilation and

2. ALI as defined by the American-European Consensus Conference criteria [1] of acute onset of:

a) Hypoxic respiratory failure (PaO2/FiO2 ≤40 kPa from two blood gases >1 hour apart).

b) Bilateral infiltrates on chest X-ray consistent with pulmonary edema. Infiltrates considered ‘consistent with pulmonary edema’ include any patchy or diffuse infiltrates not fully explained by mass, atelectasis, or effusion or opacities known to be chronic (>28 days).

c) No clinical evidence of left atrial hypertension or if measured, a pulmonary arterial occlusion pressure (PAOP) less than or equal to 18 mmHg.

All ALI criteria (a to c) must occur within the same 24 hour period. The time of onset of ALI is when the last ALI criterion is met.

Patients fulfilling any of the criteria below will be excluded from the trial:

1. Age <16 years

2. More than 48 hours from the onset of ALI

3. Patient is known to be pregnant

4. CK >10 times the upper limit of the normal range

5. Transaminases >8 times the upper limit of the normal range

6. Patients currently receiving ongoing and sustained treatment with any of the following: itraconazole, ketoconazole, HIV protease inhibitors, nefazodone, cyclosporine, amiodarone, verapamil or diltiazem.

7. Patients with severe renal impairment (estimated creatinine clearance less than 30 ml/minute) not receiving renal replacement therapy

8. Severe liver disease (Child's Pugh score >12)

9. Current or recent treatment (within two weeks) with statins

10. Physician decision that a statin is required for proven indication

11. Contraindication to enteral drug administration, for example, patients with mechanical bowel obstruction. Patients with high gastric aspirates due to an ileus are not excluded.

12. Domiciliary mechanical ventilation except for CPAP/BIPAP used for sleep-disordered breathing.

13. Known participation in other investigational medicinal product (IMP) trials within 30 days.

14. Consent declined

15. Treatment withdrawal imminent within 24 hours

16. Non-English speaking patients or those who do not adequately understand verbal or written information unless an interpreter is available.

### Power and sample size estimate

The mean (standard deviation; SD) VFDs in 432 patients with ALI was 12.7 (10.6) days [16]. The SD (10.6) for VFDs in ALI used for the sample size calculations is similar to the SD for VFDs that has been consistently reported in other large multi-center clinical trials [17-19]. There are no prospective trials in patients with ALI to predict the treatment effect size of simvastatin to improve VFDs. In a recent retrospective study, statin usage in patients with ALI was associated with a 31% increase in VFDs [20]. Our observational data showed a 37% relative improvement in mortality in patients who received a statin [4]. In our proof of concept study, OI and SOFA scores improved by 50% to 66%, respectively, in the simvastatin-treated group [11]. Pre-treatment with simvastatin decreased a range of pulmonary inflammatory mediators induced by LPS in healthy volunteers by between 34% to 65% [10]. On the basis of these data, a conservative treatment effect of 20% has been estimated for this study.

A sample size of 524 subjects (262 in each group) will have 80% power at a two-tailed significance level of 0.05 to detect a 20% difference in VFDs. To estimate loss after recruitment, previous data from the PAC-Man trial were used where 2.4% of recruited patients or their relatives subsequently withdrew their consent, or were randomized in error [21]. Thus, estimating a dropout rate of 3% the study will require a total of 540 patients with 270 in each group (Figure 1).

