### Randomization and study drug supply

Patient drug packs will be prepared by Victoria Pharmaceuticals (Belfast, UK). Simvastatin 40 mg or identical placebo tablets will be packaged in a white opaque plastic container which will be sealed with a tamper-evident seal and labelled in compliance with applicable regulatory requirements. Each container will contain 70 tablets of the study drug for the treatment of one patient for 28 days (plus 7 days overage). All trial drugs will be packaged identically and identified only by the unique trial identifier.

Patients will be randomized in a 1:1 ratio using an automated centralized 24-hour telephone or web-based randomization service (Centre for Healthcare Randomised Trials, University of Aberdeen, UK). Randomization will be stratified by site and by vasopressor requirement (defined as any inotropic requirement except dopamine <6 mcg/kg/minute). The randomization service will allocate a unique trial identifier to each patient in accordance with the computer-generated study randomization schedule. The randomization service will confirm randomization details by email to the CTU and the study site. A confirmation email will be sent to the hospital pharmacy. The clinician will complete a trial prescription form detailing the unique trial identifier assigned to the patient. The hospital pharmacy will dispense the drug pack labelled with the corresponding unique trial identifier for the patient.

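### On the article's own mean and SD, 262 per group gives about 78% power, not 80%, for an exact 20% difference in VFDs; 262 corresponds to 2.6 days (about 20.5%)

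*Protocol article*

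**What the plan says.** All the inputs are in the protocol article, under Power and sample size estimate, apart from the allocation ratio.

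- Mean and SD: "The mean (standard deviation; SD) VFDs in 432 patients with ALI was 12.7 (10.6) days". The section confirms the SD as an input: "The SD (10.6) for VFDs in ALI used for the sample size calculations".
- Effect: "a conservative treatment effect of 20% has been estimated for this study". It is given only as a percentage; no difference in days appears.
- Test level and target: "at a two-tailed significance level of 0.05 to detect a 20% difference in VFDs".
- Size and power: "A sample size of 524 subjects (262 in each group) will have 80% power at a two-tailed significance level of 0.05".
- After a 3% loss allowance: "the study will require a total of 540 patients with 270 in each group".
- Allocation is 1:1 (Randomization and study drug supply).

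**The concern.** The section states every quantity that a two-group comparison of means needs, so a reader can recompute the size directly. Doing so gives 274 or 275 per group rather than 262. The stated size, the stated power and the stated 20% therefore do not fit together on the printed mean and SD.

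What is at stake is modest. This section is the public justification of the trial's size, and a neutral result will be read beside the sentence on 80% power for a 20% difference. Because no difference in days is given, a reader will take 20% of 12.7 and cannot tell that the calculation matches a slightly larger difference.

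**Working it through.** **Inputs.** Mean 12.7 days, SD 10.6 days, 20% relative difference, two-sided alpha 0.05, power 80%, 1:1 allocation. The one assumption is that the 20% applies to 12.7, so the difference is 0.20 × 12.7 = 2.54 days.

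**1. Trying to reproduce 262.** The normal-approximation formula is n per group = 2 × (1.96 + 0.8416)² × SD² / difference².

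- 2.54 days: 2 × 7.849 × 112.36 / 6.4516 = 273.4, so 274. The t-test needs 275.
- 2.6 days: 2 × 7.849 × 112.36 / 6.76 = 260.9, so 261. The t-test needs 262, which is the stated figure.

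Other readings do not return 262:

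| Reading | n per group (normal approximation unless noted) |
|---|---|
| Difference rounded to 2.5 days | 283 (t-test 284) |
| One-sided test, 2.54 days | 216 |
| 20% of the treated mean (12.7/0.8 − 12.7 = 3.175 days) | 175 |
| 2.54 days, inflated for a rank test (274/0.955) | 287 |

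A control mean of about 13.0 would also give 262, because 0.20 × 13.0 = 2.6 days. The article gives no such mean.

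**2. Power at the stated size.** The standard error of the difference at 262 per group is 10.6 × √(2/262) = 0.926 days.

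- 2.54 days: 2.54/0.926 = 2.743, and 2.743 − 1.960 = 0.783, so power is 78.3% (normal) or 78.2% (t-test).
- 2.6 days: 80.2% (normal) or 80.0% (t-test).

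If all 270 per group were analysed, the standard error would be 10.6 × √(2/270) = 0.912 days. Power for 2.54 days would be 79.5% (normal) or 79.4% (t-test).

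**3. Difference detectable with 80% power at 262 per group.** 2.8016 × 0.926 = 2.59 days (normal) or 2.60 days (t-test), which is 20.4% to 20.5% of 12.7.

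**4. Size of the gap.**

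- Power: 80.0 − 78.2 = 1.8 percentage points.
- Patients: 274 − 262 = 12 or 275 − 262 = 13 per group, that is 12/262 = 4.6% or 13/262 = 5.0%.
- In total, 548 to 550 evaluable patients against 524.

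**5. The loss allowance.** 524/0.97 = 540.2 and 540 × 0.97 = 523.8, so the step from 524 to 540 is sound. For comparison only, 548/0.97 = 565 and 550/0.97 = 568 (rounded up).

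**The case against.** The strongest reply is that this is rounding. 2.6/12.7 = 20.47%, which prints as 20% at the whole-percent precision that the section uses. On that view the article only lacks a figure in days, which the full protocol may give. This stands as an account of how small the problem is. It does not make the sentence right, because a reader given 12.7 and 20% will compute 2.54. Rounding of the printed mean and SD does not close the gap either: a mean of 12.75 with an SD of 10.55 still needs 270 per group by t-test.

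A second reply is that the gap is lost in the uncertainty of the inputs. If the SD of 10.6 from 432 patients is treated as a normal-sample estimate, its 95% interval is about 9.94 to 11.36. The required size for 2.54 days then runs from 273.4 × (9.94/10.6)² = about 240 to 273.4 × (11.36/10.6)² = about 314 per group. This also stands, and is why no change of sample size follows.

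A third reply is that 78% belongs to a t-test on means, whereas the article's Statistical analysis plan section intends to compare medians. That is correct. The 78% corrects the stated calculation and does not give the power of the planned analysis, so any restated sentence should name its test.

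Some stronger readings are tempting but not supported:

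- **The design lacks its headline power.** The shortfall is 1.8 points, and a neutral result will be judged by its confidence interval, which the article plans to report.
- **2.54 was rounded up to 2.6.** Ordinary rounding gives 2.5, and another control mean would explain 262 equally well. The cause cannot be settled from the article.
- **Covariate adjustment would recover the shortfall.** The article mentions covariates only for the other continuous outcomes and gives no prognostic strength from which a gain could be computed.

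**Conclusion.** The point holds as a low-severity correction of a stated figure. With SD 10.6 and two-sided 0.05, 262 per group gives about 78% power for an exact 20% (2.54-day) difference. The stated 80% belongs to 2.6 days, about 20.5%. This rests on two assumptions: that the 20% is relative to 12.7, which the section implies but does not say, and that the calculation was a two-sample comparison of means. If another base was used, the size may be right, but the section then omits the input that produced it.

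A reader might infer that the trial should recruit about 565 to 568 patients, or that 540 is an error. Neither follows: the loss step is correct, and so small a difference in power does not justify enlarging the trial.

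**What to change.** Keep 524 evaluable and 540 recruited, and restate the power sentence in days, for example:

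> With 262 patients per group there is 80% power (two-sample t-test, SD 10.6 days, two-sided 0.05) for a difference of 2.6 days in mean VFDs, about 20.5% of 12.7; for exactly 20% (2.54 days) the power is about 78%.

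If the calculation used a control mean other than 12.7, state that mean and the resulting difference in days instead.

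The cost is one sentence and a slightly less favourable power figure for exactly 20%. No patients, analyses or decision rules change.

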**Figure 1 F1:**
[figure not shown]
HARP-2 trial flow diagram.

## Trial conduct

### Consent

Informed consent will be obtained prior to conducting any trial specific procedures.

Critically ill sedated patients do not have the capacity to give consent; therefore, consistent with requirements of the EU clinical trial directive, we will obtain written informed consent/assent from a representative in keeping with regulatory requirements before randomization. All surviving patients will be informed about the trial at the earliest opportunity after regaining competence and consent to continue in the trial will be sought. The consent from the representative will remain valid until a decision on consent to continue is obtained from the patient.

